**Figure 1. LTA4H genotype modulates susceptibility to mycobacterial infection**

*
[figure not shown]
*

Zebra fish at both poles of the inflammatory response (minor and major allele homozygotes) were unable to control mycobacterial replication within granulomas, whereas those fish with an intermediate inflammatory response (the heterozygotes) controlled the infection. The phenotype of the homozygous fish could be changed to that of the heterozygotes through the respective addition of pro-inflammatory leukotriene B4 (LTB4) or TNF-α to LTA4H low fish, or by inhibition of TNF-α in the LTA4H high fish by either aspirin or dexamethasone [^19^](#_ENREF_19). Furthermore, in Vietnamese adults recruited to the earlier dexamethasone trial, only major allele homozygous adults with the hyper-inflammatory phenotype benefited from dexamethasone (**Figure 2**). Indeed, dexamethasone treatment of those with a hypo-inflammatory phenotype appeared to be detrimental.

**Figure 2. LTA4H genotype influences survival from TBM in all patients (A), pre-treatment CSF leucocyte counts (B), and survival in those who did not (C) and did (D) receive adjunctive dexamethasone.**

[figure not shown]

These findings need replication in a different population, and such studies are currently underway at OUCRU, but they provide an elegant potential explanation for the previous failure to find the mechanism by which corticosteroids improve survival from TBM in Vietnamese adults. They also have important implications for the current pilot study and we will investigate the influence of LTA4H genotype on aspirin’s effect on CSF inflammation and clinical outcome.

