**Why do we need this pilot study?**

There are several outstanding questions that need to be addressed by a pilot study before embarking on a large, definitive, randomised controlled trial of adjunctive aspirin for TBM. These are:

1. What is the safety and tolerability of 81mg and 1000mg dose aspirin when added to dexamethasone for the first 60 days of treatment of TBM?
2. Does aspirin at these doses reduce MRI-proven infarction and neurological sequelae or death?
3. Does 81 mg aspirin daily have the same anti-inflammatory effect as 1000 mg aspirin daily (assessed by measurement of CSF prostaglandins) and which dose is likely to be most effective?
4. How does host genotype (in particular, LTA4H genotype) influence the anti-inflammatory, anti-thrombotic, and clinical effects of aspirin?

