## Secondary Objectives

To determine whether host genotype, including LTA4H genotype, influences any of the above therapeutic effects of aspirin

To determine whether innate host peripheral blood monocyte/macrophage antimicrobial activity influences outcome from TBM and varies through treatment

To assess the plasma pharmacokinetics of aspirin

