## Description of Statistical Methods

The risk of clinically significant upper-gastro-intestinal bleeding and image-proven cerebral bleeding by 60 days will be summarized as x/n (%) in each group together with two-sided 95% Wilson confidence intervals and corresponding confidence intervals for risk differences between groups.

The risk of the primary efficacy endpoint of new MRI-proven brain infarction or death by 60 days will be summarized in the same way. In addition, we will perform a linear trend test for group differences based on logistic regression with adjustment for gender, MRC grade, and age.

The risk of disability or death will be summarized as for the primary efficacy endpoint and the analysis of overall survival during 240 days will be based on Kaplan-Meier graphs and Cox regression. The frequency of adverse events in each study arm and resolution of CSF inflammation will be analysed descriptively.

Analyses to explore the effect of LTA4H genotype will include this information as an additional covariate in the regression models.

As this is a pilot study of relatively small size and limited power, p-values will be interpreted with caution and a one-sided p-value <0.1 will be regarded as mild evidence for an effect. Corresponding two-sided 95% confidence intervals will be provided for all tests to assess the range of plausible magnitudes of effects given the data.

No imputation of missing data will be performed. For the analysis of GI/cerebral bleeding by day 60, patients lost to follow-up before day 60 (without prior GI bleeding) will be excluded from the analysis to get a conservative estimate of the true proportion of bleeding in the aspirin groups. The analysis of the primary efficacy endpoint will exclude patients with missing baseline or follow-up MRI scans (except for prior death).

All analyses will analyze patients according to their randomized treatment group.

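### The genotype objective asks whether LTA4H changes aspirin's effect, but the only stated genotype analysis adds LTA4H as a covariate and has no term for that question

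*Protocol*

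**What the plan says.** The objective in section 4.2 is worded as effect modification: "To determine whether host genotype, including LTA4H genotype, influences any of the above therapeutic effects of aspirin". The synopsis carries a shorter version. Section 3 puts the same question twice. It is the fourth of the questions that justify the pilot: "How does host genotype (in particular, LTA4H genotype) influence the anti-inflammatory, anti-thrombotic, and clinical effects of aspirin". The LTA4H part of the background also makes a commitment: "we will investigate the influence of LTA4H genotype on aspirin’s effect on CSF inflammation and clinical outcome".

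Section 9.2 names the models. For the primary efficacy endpoint, "we will perform a linear trend test for group differences based on logistic regression with adjustment for gender, MRC grade, and age". For survival, "the analysis of overall survival during 240 days will be based on Kaplan-Meier graphs and Cox regression". Resolution of CSF inflammation is to be analysed descriptively. One sentence then covers genotype: "Analyses to explore the effect of LTA4H genotype will include this information as an additional covariate in the regression models". The protocol mentions no interaction, stratified analysis or genotype subgroup analysis anywhere.

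**The concern.** A covariate and an effect modifier answer different questions. Adding genotype to the logistic or Cox model asks whether outcome differs by genotype at a given treatment. The objective asks whether the treatment effect differs by genotype. A model without a product term assumes that it does not.

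The background shows why this matters to the investigators. In the earlier dexamethasone trial, "only major allele homozygous adults with the hyper-inflammatory phenotype benefited from dexamethasone", and "dexamethasone treatment of those with a hypo-inflammatory phenotype appeared to be detrimental". If aspirin behaved at all similarly, the planned model would blend the effects into one figure, and the pilot would reach the design of a larger trial without the estimate it set out to obtain. CSF inflammation is a further gap. The background promises to examine genotype there too, but it has no regression model to which a covariate could be added.

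**Working it through.** **Plan's own figure.** The protocol gives none for the genotype analysis. As a check on the set-up, its trend-test power was reproduced first. Inputs from section 9.1: 40 per arm, control risk 40%, best arm 20%, third arm 20-40% (midpoint 30% taken). With centred scores −1, 0, 1 in order of assumed response:
- expected trend = 40 × (0.40 − 0.20) = 8
- null variance = 40 × 0.30 × 0.70 × 2 = 16.8 (SD 4.10)
- alternative variance = 40 × (0.24 + 0.16) = 16 (SD 4)
- power at one-sided 10% = Φ((8 − 1.282 × 4.10)/4) = 75%; at one-sided 2.5% = Φ((8 − 1.960 × 4.10)/4) = 50%

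Both agree with the stated approximate values.

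**Model forms.** Let t be the arm score (0, 1, 2) and g the genotype group (0, 1).
- Covariate model: logit p = α + βt + γg. The aspirin log odds ratio per step is β in every genotype.
- Interaction model: logit p = α + βt + γg + δtg. It is β when g = 0 and β + δ when g = 1.

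The objective concerns δ, which the covariate model fixes at zero. The same holds for log hazard ratios in the Cox model.

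**Illustration.** Both models were fitted to expected cell counts for N = 120. The documents give no genotype shares, so the share of the responsive genotype was assumed to be 20%, 35% or 50%, with two groups and no other covariates. Risks in the responsive genotype were 40/30/20% across the ordered arms. In the other genotype they were either flat at 40% (one genotype benefits) or 20/30/40% (full reversal). Power = Φ(|δ|/SE − z).

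| Scenario | Share | Covariate model: treatment OR per step | Covariate model: genotype OR | Interaction model: OR per step, other / responsive | SE of δ | Power, 10% | Power, 2.5% |
|---|---|---|---|---|---|---|---|
| One benefits | 20% | 0.92 | 0.64 | 1.00 / 0.61 | 0.619 | 31% | 12% |
| One benefits | 35% | 0.86 | 0.64 | 1.00 / 0.61 | 0.512 | 37% | 16% |
| One benefits | 50% | 0.80 | 0.64 | 1.00 / 0.61 | 0.481 | 39% | 17% |
| Reversal | 20% | 1.33 | 1.00 | 1.63 / 0.61 | 0.631 | 60% | 34% |
| Reversal | 35% | 1.15 | 1.00 | 1.63 / 0.61 | 0.529 | 71% | 45% |
| Reversal | 50% | 1.00 | 1.00 | 1.63 / 0.61 | 0.505 | 74% | 49% |

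Example, one genotype benefits, 50% share: δ = ln 0.614 = −0.488; 0.488/0.481 = 1.01; Φ(1.01 − 1.282) = 39%.

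**Reading the table.**
- Under reversal at a 50% share, the covariate model shows nothing at all.
- When one genotype alone benefits, both genotypes have the same placebo risk (40%), yet the covariate model gives a genotype odds ratio of about 0.64. That looks like prognosis but comes wholly from the treatment difference.
- The 95% interval for the ratio of odds ratios runs from the estimate divided by a factor to the estimate times that factor. The factor is exp(1.96 × 0.481) = 2.6 at best and exp(1.96 × 0.631) = 3.4 at worst.

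The reversal scenario does not keep the protocol's 40% control risk: at a 50% share the placebo risk is 0.5 × 40% + 0.5 × 20% = 30%. It shows the mechanism and is not a forecast.

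**The case against.** The best reply has three parts.

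**It is secondary and exploratory.** The sentence speaks of exploring, the trial is a 120-patient pilot, and section 9.2 already asks for caution with p-values and for confidence intervals. No primary endpoint, primary analysis or sample size depends on it. This stands and limits the severity.

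**The SAP can add an interaction.** It can: the SAP is not at hand, and baseline blood for genotyping is taken from every patient, so nothing is lost. But the protocol is not silent here. It names a method, and that method does not estimate what section 4.2 asks. To say that a covariate loosely includes a product term goes beyond the wording, which adds genotype to models already described by their adjustment terms.

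**The trial is too small for interactions.** Power is indeed low. That argues for estimates with intervals, not for estimating a different quantity.

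Some stronger readings should be resisted:
- A reader might infer that the background predicts benefit from aspirin in one genotype and harm in another. It does not. The human pattern is for dexamethasone, the protocol says it needs replication, the aspirin evidence is from zebrafish with high LTA4H, and all trial patients receive dexamethasone.
- A reader might infer that coding genotype by allele count is an error in the plan. No coding is stated.
- A reader might infer that the pilot would misdirect the definitive trial. The documents do not support that: the primary results are unaffected and genotype-specific estimates remain obtainable.

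**Conclusion.** The point holds as a mismatch between a stated objective and its stated method, and should be fixed. That conclusion rests on model form alone and on no assumed number. An additive covariate gives a prognostic genotype effect and one common aspirin effect, so the section 4.2 question goes unanswered if section 9.2 is followed as written. The CSF part of the question is not reached at all.

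The size is illustrative. It depends on assumed genotype shares of 20-50%, two genotype groups and the assumed risks. On those terms the pooled odds ratio per step lies between 0.80 and 0.92 when the truth is 1.00 in one genotype and 0.61 in the other, and it can be exactly 1.00 under full reversal. Even the right model would often miss a real difference: power at one-sided 10% is about 31-39% if one genotype benefits and 60-74% under reversal. The gain from the fix is an estimate of the right quantity with an honest interval, not a decisive test.

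**What to change.** Replace the genotype sentence in section 9.2 with: *LTA4H genotype will be included with a treatment-by-genotype interaction in the logistic and Cox models, and treatment effects will be reported within genotype groups with 95% confidence intervals, as exploratory.*

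Add that the CSF inflammation summaries will be shown by arm within genotype, so that the commitment in the background is also met.

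Pooling the two aspirin doses against placebo is optional and could serve as a supportive analysis to limit sparse cells. It should not be the required analysis, because the protocol itself asks whether the two doses differ in anti-inflammatory effect.

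The cost is wording only, since the blood is already collected. The downside is wide intervals, above all in the rarest genotype, so the report should stress estimates and intervals over the interaction p-value. The change should be made before unblinding, so that the interaction model is not a post hoc choice.

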## Primary and Secondary Endpoints/Outcome Measures

The primary safety endpoint will be the occurrence of clinically significant upper-gastro-intestinal bleeding and any cerebral bleeding confirmed by brain imaging by 60 days from randomisation.

Clinically significant upper gastro-intestinal bleeding will be defined as any one of the following:

1. Vomiting fresh or changed blood of any volume
2. Melena
3. Unexplained drop in haemoglobin concentration of >2g/L
4. Greater than 5mls of fresh or changed blood aspirated from nasogastric tube

The primary efficacy endpoint will be any new MRI-proven brain infarction or death by 60 days. To assess this endpoint MRI will need to be taken at baseline and at 60 days from randomisation. The scans will be read by an independent neuroradiologist blind to the treatment allocation.

The secondary endpoints will be:

- Number of grade 3&4 and serious adverse events by day 60 from randomisation
- Time to death during 240 days from randomisation
- Duration of hospital stay
- Neurological disability (as assessed by the modified Rankin score and Glasgow outcome score) by days 60 and 240.
- Resolution of CSF inflammation by day 30 through measurement of CSF leucocytes, protein, glucose, cytokines (TNF-α, IL-1β, IL-8, IL-10, IFNγ) and eicosanoids (15-epi-Lipoxin, Lipoxin A4, LTB4, PGE2, TBXB2, PGD2).
- Antimicrobial activity of peripheral blood monocyte/macrophages on day 240 compared to baseline.
- The proportion of patients with MRI-proven infarction by day 240
- Concentration-time profile of salicylic acid including exposure, peak levels, half-life, elimination clearance and volume distribution

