# STATISTICS

## Sample size justification

Sample size was chosen based on clinical and feasibility considerations. The calculations below provide evidence of what can be achieved with a sample size of 40 patients per group for the primary safety and efficacy endpoints, respectively.

The proportion of HIV uninfected patients with clinically significant gastro-intestinal bleeding from our on-going 05TB trial of hyper-intensive anti-tuberculosis chemotherapy in Vietnam is about 1% (3/278). Cerebral bleeding associated with TBM is extremely rare (estimated at <0.01% of all patients), but it is possible it may be more common in those treated with aspirin. We have, therefore, included in the primary assessment of safety.

Assuming no effect of aspirin on gastrointestinal bleeding, i.e. a true gastrointestinal bleeding risk of 1% for aspirin, the probability will be 67% to observe 0/40 patients and 27% to observe 1/40 patient experiencing gastrointestinal bleeding in each aspirin arm. The corresponding upper limits of the 95% confidence intervals for the risk of a gastrointestinal bleed would allow “proving” that the true gastrointestinal bleeding risk for aspirin is (at worst) ≤8.8% (in case of 0/40 observed gastrointestinal bleeding) or ≤12.9% (in case of 1/40 observed gastrointestinal bleeding).

Assuming further equal gastrointestinal bleeding risks of 1% in the combined aspirin groups, the probability will be 80% that we observe zero or one bleeding event amongst the 80 patients receiving aspirin and the corresponding upper limit of the 95% confidence interval for the risk of a bleed would allow “proving” that the true overall bleeding risk for aspirin is (at worst) ≤6.8%.

If in contrast, the risk of bleeding was increased to 10% in one of the aspirin arms, the probability would be 78% that we observe 3/40 patients with gastrointestinal bleeding or more with a corresponding 95% confidence interval that would “prove” that the true bleeding risk for that aspirin arm were (at best) ≥2.5%.

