The trial protocol will seek ethical approval to include incapacitated/comatose adults in the trial as we consider many of these adults will have the most severe infection and therefore represents the group that might stand most to gain from aspirin. We anticipate around 50% of patients be critically ill with reduced consciousnnes and unable to consent for themselves. Once incapacity has been confirmed by one of the ward physicians, written informed consent will be sought from the patient’s relative/representative. If the subject regains capacity during treatment they will be informed of the consent given by their representative and their wishes respected concerning on-going participation. If they are happy to remain in the trial, the patient should sign and date two copies of an informed consent form at this time. If they wish to withdraw from the trial, no further trial-related procedures will be performed, but data to this point would be used in analysis. Data from any patient who dies before regaining capacity (but whose representative has provided consent) will be included in analysis.

Patients’ confidentiality will be maintained throughout the trial. Data submitted to OUCRU Clinical Trials Unit and samples sent to central testing facilities will be identified only by the trial number and patient initials.

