5. MRI brain can be +/- 5 days from randomisation and the date of follow-up.
6. Active surveillance for known adverse reactions to aspirin, including gastro-intestinal bleeding, renal dysfunction, and hepatitis. Cerebral bleeding will be assessed on MRI brain performed at baseline and day 60.
7. Only necessary if screening blood is >48 hours prior to baseline

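### The loss-to-follow-up rule for the primary safety analysis exempts only prior GI bleeding, so a confirmed cerebral bleed in a patient later lost is dropped

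*Protocol*

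**What the plan says.** Protocol section 5.2 (Primary and Secondary Endpoints/Outcome Measures) gives the primary safety endpoint two components: clinically significant upper GI bleeding, and "any cerebral bleeding confirmed by brain imaging by 60 days from randomisation". Either one is an endpoint event.

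Section 9.2 (Description of Statistical Methods) summarises the risk by arm with two-sided 95% Wilson intervals. Its missing-data paragraph opens with "No imputation of missing data will be performed". It then sets a rule whose scope is both components, "For the analysis of GI/cerebral bleeding by day 60", and which reads: "patients lost to follow-up before day 60 (without prior GI bleeding) will be excluded from the analysis to get a conservative estimate". The estimate meant is the true proportion bleeding in the aspirin groups.

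Section 12.4 (Risks and Benefits) deals with patients enrolled through a representative who regain capacity and choose to leave: "no further trial-related procedures will be performed, but data to this point would be used in analysis".

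**The concern.** The rule's scope covers GI and cerebral bleeding, but its exception covers GI bleeding alone. A patient who has already had a confirmed cerebral bleed and is then lost therefore falls under the exclusion. A primary safety event that has been observed and confirmed is removed, and the patient with it.

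For a rule described as conservative, the error goes the wrong way: it makes aspirin look safer. It also falls on the component that section 9.1 added to the endpoint because aspirin might make it more common. With 40 patients per arm, one event is enough to move the result between two of the protocol's own worked safety statements.

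**Working it through.** **Inputs.** Arm size: "a sample size of 40 patients per group" (section 9.1). Interval: two-sided 95% Wilson (section 9.2). Loss rate: not stated, so the cases below are illustrations. Assumption: a patient who withdraws completely before day 60 counts as lost, since section 9.2 does not define the term.

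**Formula.** With p = x/n and z² = 3.8415, the Wilson upper limit is [p + z²/(2n) + z·√(p(1−p)/n + z²/(4n²))] / (1 + z²/n). For x = 0 it reduces to z²/(n + z²).

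**The protocol's own figures.**
- 0/40: 3.8415/43.8415 = 8.76% (stated 8.8%).
- 1/40: (0.0250 + 0.0480 + 1.96 × 0.03478)/1.0960 = 12.88% (stated 12.9%).
- 1/80: 6.75% (stated 6.8%).

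The method reproduces the plan.

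**One patient with a cerebral bleed, then lost, in an arm of 40.**

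| GI bleeds in the arm | Rule as written | Event kept |
| --- | --- | --- |
| 0 | 0/39 = 0%, upper 8.97% | 1/40 = 2.5%, upper 12.88% |
| 1 | 1/39 = 2.6%, upper 13.18% | 2/40 = 5.0%, upper 16.50% |
| 2 | 2/39 = 5.1%, upper 16.89% | 3/40 = 7.5%, upper 19.86% |

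The estimate falls by 2.4 to 2.5 percentage points and the upper limit by 3.0 to 3.9 points.

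The direction does not depend on the example. With g other events, (g+1)/40 exceeds g/39 whenever 39(g+1) > 40g, that is, for every g below 39.

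**Where the rule is conservative.** Suppose one event is kept and four bleed-free patients are lost. Excluding those four gives 1/36 = 2.8% (upper 14.17%), against 1/40 = 2.5% (upper 12.88%) if they were counted as event-free. For this group the stated aim is met.

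**Both together.** Four bleed-free patients are lost, and a fifth is lost after a cerebral bleed. As written: 0/35, upper 9.89%. With the event kept: 1/36, upper 14.17%. With everyone counted: 1/40, upper 12.88%. Here the conservative part of the rule does not make up for the dropped event.

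**The case against.** The case for leaving the text alone is that the intent is clear. The sentence begins with both components, so a sensible analyst would keep anyone with a prior endpoint event. Section 12.4 retains data up to withdrawal. The trigger is also narrow: the bleed must be imaged before day 60, the patient must survive (death is not loss to follow-up), and then be lost before day 60. Patients taken off study drug by the investigator are still followed under section 6.5. Background cerebral bleeding is put below 0.01% in section 9.1. A bleed would still be recorded as an adverse event under section 8.3.

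Most of this stands, and it limits the weight of the point. It does not remove it. Section 12.4 covers only patients who regain capacity and withdraw. Adverse event listings do not repair the primary safety proportion. A rule fixed in advance should not rely on the analyst departing from its wording.

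A reader might infer something stronger. Appendix B says "Cerebral bleeding will be assessed on MRI brain performed at baseline and day 60", and section 9.2 excludes missing scans only for the efficacy endpoint. From this it could seem that patients who die or attend without a day-60 MRI are counted as free of cerebral bleeding. The document does not support that. It never says how such patients are classified in the safety analysis, and that is commonly left to a statistical analysis plan, which is not at hand. Never-imaged patients who are lost are excluded, not counted as bleed-free. Section 5.2 accepts any brain imaging by day 60, so a scan done for clinical reasons can establish the event without the scheduled MRI. Any estimate of the effect would need an unimaged share and a true cerebral bleeding risk that the protocol does not give.

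Nor is a denominator restricted to imaged patients a clear improvement. It conditions on surviving to a scan, which may differ by arm. If, as an assumption, 40% of an arm had no scan, n would fall to 24 and the zero-event upper limit would rise from 8.8% to 3.8415/27.8415 = 13.8%.

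**Conclusion.** The point holds for the wording of the exception. As written, the rule deletes a confirmed primary safety event when a patient with a cerebral bleed is later lost, and this contradicts the conservative aim given in the same sentence. One such patient in an arm of 40 lowers the estimate by about 2.5 points; with no other event the upper limit drops from 12.9% to 9.0%. That is close to the gap between the protocol's own statements for one and for no events.

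This rests on a literal reading, on complete withdrawal counting as loss, and on at least one patient following that sequence. Such a patient is likely to be rare, and the rule remains conservative for lost patients with no bleed. It is a minor correction to a stated analysis rule. It does not extend to how patients without imaging are counted.

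**What to change.** In section 9.2, replace the bracketed exception with: *without a prior primary safety endpoint event (GI or cerebral bleeding)*. This is a change of one phrase. It needs no new data and leaves the sample size and interval method as they are.

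If the team wants the cerebral component to be easier to interpret, it could also report, by arm, the number of patients without post-baseline brain imaging, including deaths. That costs one descriptive line, and the primary denominator would not change.

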***Clinical data supporting a role for aspirin in TBM treatment***

Two recent clinical studies suggest aspirin is safe when added to dexamethasone and may improve outcome from TBM. The first study randomised 118 Indian adults with TBM to standard anti-tuberculosis chemotherapy, with or without aspirin (150mg daily)[^16^](#_ENREF_16). The investigators hypothesised that aspirin would reduce the incidence of stroke and the primary endpoint was MRI-proven infarction by 3 months, with or without neurological deficit. By 3 months, MRI proven stroke occurred in 21 (33.3%) of all patients: 13 (43%) in the placebo arm and 8 (24%) in the aspirin group (P=0.18). Aspirin was associated with a significant reduction in mortality (43% versus 21.7%, P=0.02). The incidence of adverse events was not significantly different between the treatment groups and, in particular, there was no aspirin-associated gastro-intestinal bleeding reported. The results are hard to interpret, however, because of the variable use of prednisolone across the treatment arms. Prednisolone was given for severe disease at baseline, or if a patient’s condition worsened after the start of treatment. Any effect of aspirin, especially on mortality, is hard to disentangle from that of the corticosteroids.

A second study randomised 146 South African children with TBM to standard anti-tuberculosis chemotherapy plus placebo (n=50), low-dose aspirin (75mg/24 hours) (n=47), or high-dose aspirin (100mg/kg/24hours) (n=49) [^17^](#_ENREF_17). Aspirin has no significant impact on survival, but 9 children developed hemiplegia after the start of treatment and none of them received high-dose aspirin. Furthermore, the children in the high-dose aspirin group were significantly younger with more severe disease than the other treatment groups, yet their neurological outcomes were similar. Two children stopped aspirin early: one because of haematemesis and the other because of cerebral haemorrhage. Whether these patients received high or low dose aspirin was not reported.

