We expect a risk of new MRI-proven brain infarction or death within 60 days of approximately 40% in the control arm. Based on the results of the trial performed by Misra et al ^16^, we assume that 81 mg aspirin daily may halve this risk to 20% and the risk in the 1000 mg aspirin daily arm is between 20-40%, then a linear trend test across the 3 groups will have approximately 75% power to detect such an effect at the one-sided 10% significance level (i.e. to generate “mild evidence”) and approximately 50% power to detect it at the conventional one-sided 2.5% significance level.

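### The primary efficacy analysis keeps every death but drops survivors without both MRIs, so the analysis set depends on the outcome and the quoted power holds only if nobody is dropped

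*Protocol*

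**What the plan says.** Section 5.2 defines the outcome: "The primary efficacy endpoint will be any new MRI-proven brain infarction or death by 60 days". It requires scans at baseline and day 60 to assess it.

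Section 9.2 fixes who is analysed. It says "No imputation of missing data will be performed" and then "The analysis of the primary efficacy endpoint will exclude patients with missing baseline or follow-up MRI scans (except for prior death". It ends with "All analyses will analyze patients according to their randomized treatment group". That last sentence settles the grouping, but it does not put every randomised patient in the analysis.

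Section 9.1 describes "what can be achieved with a sample size of 40 patients per group for the primary safety and efficacy endpoints". For efficacy it says "We expect a risk of new MRI-proven brain infarction or death within 60 days of approximately 40% in the control arm", assumes 20% on 81 mg and 20-40% on 1000 mg, and quotes about 75% power (one-sided 10%) and about 50% (one-sided 2.5%). It makes no allowance for patients the section 9.2 rule would remove.

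Section 6.4.4 allows the baseline MRI up to 5 days after randomisation, so either scan can be lost after randomisation.

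**The concern.** Inclusion depends on a component of the outcome. Patients who die need no scan and are all events. Survivors, most of them non-events, leave the denominator if either scan is missing. The arm risks can therefore be biased even when scans are lost purely by chance among survivors. Deaths gain weight relative to infarcts, although preventing infarction is a main part of the rationale in section 3.

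The rule is also unclear about events already known. It makes no stated exception for a survivor with a new infarct on an unscheduled MRI but no day-60 scan. The bleeding rule in the same section does keep patients who bled before being lost.

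At stake are the arm risks and risk differences that section 9.2 reports directly, and which the pilot exists to supply for a definitive trial.

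**Working it through.** **Inputs.** From section 9.1: 40 per arm; risks of 40% (placebo), 20% (81 mg) and 20-40% (1000 mg; midpoint 30% used). Assumed, because the protocol gives neither: the split of events into deaths and infarcts, and m, the share of survivors lacking a usable scan pair.

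**1. Reproducing the stated power.** Cochran-Armitage trend test, equally spaced scores, arms ordered placebo, 1000 mg, 81 mg (section 9 does not fix the scores; the stated figures reproduce across the 20-40% range in this order).
- Expected statistic: 40 × (0.40 − 0.20) = 8.
- Null variance: 0.3 × 0.7 × 80 = 16.8 (SD 4.10).
- Alternative variance: 40 × (0.24 + 0.16) = 16 (SD 4).
- One-sided 10%: Φ[(8 − 1.282 × 4.10)/4] = 75.4%.
- One-sided 2.5%: Φ[(8 − 1.960 × 4.10)/4] = 49.7%.

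The stated figures are reproduced with all 40 per arm evaluable.

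**2. Risk under the rule.** Let d be the death risk and i the risk of surviving with a new infarct, both as shares of all patients. If m is unrelated to infarction:

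observed risk = [d + i(1−m)] / [d + (1−d)(1−m)]; true risk = d + i.

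With half of events deaths, placebo has d = i = 0.20 (infarcts in 25% of survivors) and 81 mg has d = i = 0.10.

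| m | Placebo (true 40%) | 81 mg (true 20%) | Difference (true 20 points) |
|---|---|---|---|
| 10% | 0.38/0.92 = 41.3% | 0.19/0.91 = 20.9% | 20.4 |
| 20% | 0.36/0.84 = 42.9% | 0.18/0.82 = 22.0% | 20.9 |
| 30% | 0.34/0.76 = 44.7% | 0.17/0.73 = 23.3% | 21.4 |

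**3. Where the effect lies (m = 20%, placebo 42.9%).**
- Aspirin halves death only (20% to 10%, infarct still 25% of survivors): true difference 7.5 points; observed 42.9% − 0.28/0.82 = 8.7.
- Aspirin cuts infarct in survivors only (25% to 10%): true 12 points; observed 42.9% − 0.264/0.84 = 11.4.
- Limiting cases with a true difference of 20 points: 22.9 if all on death, 19.0 if all on infarction.

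**4. Odds ratio.** Observed odds = [d/(1−m) + i]/(1−d−i). If deaths are a share s of events in every arm and m is equal, this is the true odds × [s/(1−m) + 1 − s]. The factor cancels, so the odds ratio stays 0.375. In the limiting cases of step 3 it becomes 0.333 (death only) or 0.417 (infarct only).

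**5. Direction.** If survivors with infarcts miss scans at rate a and the others at rate b, the bias vanishes when a/b = (d+i)/i, which is 2 when half of events are deaths. With 20% v 10%, the observed placebo risk is 40.0%; with 30% v 10%, 38.6%.

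**6. Unequal loss with no drug effect (40% in both arms).** Missing 10% v 20% creates 42.9 − 41.3 = 1.6 points; 10% v 30% creates 44.7 − 41.3 = 3.4 points.

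**7. Power under the rule (half of events deaths, 1000 mg risk 30%).** Step 1 repeated with the observed risks and reduced numbers (at m = 20%: 33.6, 33.2 and 32.8 evaluable on placebo, 1000 mg and 81 mg):

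| m | One-sided 10% | One-sided 2.5% |
|---|---|---|
| 0 | 75.4% | 49.7% |
| 10% | 73.3% | 47.0% |
| 20% | 70.9% | 44.2% |
| 30% | 68.3% | 41.2% |

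With deaths making up 25-75% of events, the m = 20% row ranges over 69.7-72.1% and 42.8-45.5%.

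**The case against.** The strongest reply is that the effect is small and its size is assumed. A shift of 1 to 3 points compares with a 95% confidence half-width of about 1.96 × √(0.24/40 + 0.16/40) = 19.6 points. Section 9.1 says the sample size rests on clinical and feasibility grounds, so no power target is missed, and section 9.2 treats p-values cautiously. Section 6.3 excludes patients unlikely to get the early scan, section 6.5 keeps following patients whose study drug is stopped, and section 12.4.1 pays for visits and travel. All of this stands and limits the size. None of it changes the rule, and the entry criterion does not protect the day-60 scan.

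Exclusion of a known infarct is also not explicit. Section 9.2 refers to follow-up scans rather than to the day-60 scan, and section 5.2 counts any new infarct. That is fair: the wording is ambiguous and needs settling.

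Two stronger readings are tempting and are not supported:
- **The risk is always overstated.** Disabled survivors with infarcts may miss scans more often, and step 5 shows the bias can then cancel or reverse.
- **Nearly half of patients will be unevaluable.** For the cited adult trial, section 3 says "MRI proven stroke occurred in 21 (33.3%) of all patients: 13 (43%) in the placebo arm and 8 (24%) in the aspirin group". This implies 13/0.43 ≈ 30 plus 8/0.24 ≈ 33, or 63 of 118 randomised. A reader might infer 47% loss and about 21 evaluable per arm here. But this protocol's rule counts deaths as evaluable, and that trial's mortality was 43% v 21.7%. Those percentages fit 25/58 and 13/60 (an inference), giving 38 deaths and 80 survivors. If the 63 were survivors, which section 3 does not say, 17/80 = 21% of survivors were unscanned and 101/118 = 86% would be evaluable, or about 34 of 40.

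**Conclusion.** The point holds in moderate form. As written, the rule makes the primary efficacy analysis set depend on the outcome. It biases the arm risks even when scans are lost purely by chance among survivors: upward if loss is unrelated to infarction, and possibly not at all or downward otherwise. It exaggerates an effect on death and dilutes one on infarction. The odds ratio behind the trend test escapes only if loss is equal and deaths form the same share of events in each arm. The power loss is modest: about 2 points at 10% and 4 to 5 at 20% of survivors unscanned for the one-sided 10% test. Every size here rests on an assumed missing-scan rate and event split. The fault is worth correcting because it is written into the primary analysis and cheap to remove, but it does not undermine the trial.

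**What to change.** 1. **Known infarcts.** State that a new infarct documented on any MRI by day 60 counts as an event even if the day-60 scan is missing. This agrees with section 5.2 and parallels the bleeding rule.
2. **Analysis set.** Estimate the composite on all randomised patients with known day-60 vital status, as death risk + (1 − death risk) × infarct risk in survivors. Obtain the infarct risk from scanned survivors by inverse-probability weighting, or by a small imputation model with arm, MRC grade and age. A richer within-arm model would be unstable: the placebo arm would have only about 40 × 0.8 × 0.25 = 8 survivors with infarcts. Keep the present complete-case rule and best/worst-case bounds as sensitivity analyses. Report missing scans and unknown vital status by arm.
3. **Power.** Say in section 9.1 that 75%/50% applies to 40 evaluable per arm, and add about 73/47% and 71/44% for 10% and 20% of survivors unscanned. These describe the current rule; recompute them for the estimator chosen.

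The cost is wording and modest programming. The new analysis assumes scans are missing at random among survivors given those covariates, which cannot be verified, and the stated power becomes slightly lower.
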